#### Exit survey

At the end of each intervention an exit survey will be administered to capture further insight and qualitative information about participant perceptions of the diets. The surveys will ask participants to elaborate what they enjoyed and found challenging about the diet they have just completed. To measure hunger and satiety experienced during each intervention the survey will also include five questions based on the 5-Factor Satiety Questionnaire [69] with corresponding visual analogue scales (VAS). Participants will be asked to indicate 1) “How hungry did you feel after you finished a meal?”, 2) “How full did you feel after you finished a meal”, 3) “How satisfied did you feel after you finished a meal?”, 4) “How strong was your desire to eat after you finished a meal?” and 5) “How much more could you have eaten after you finished a meal?”. For questions 1-4, the VAS will range from “Not at all” to “Extremely”, and for question 5 the VAS will range from “Nothing at all” to “A very large amount”.

### Procedure

Data will be collected by participants at home and by study personnel during clinic assessment visits at the SIHR CTF across the course of the trial (See Fig. 2).

**Fig. 2 Fig2:**
[figure not shown]
Title: Schedule of enrolment, interventions, and assessment. Legend: *Bi-weekly. Med diet, Mediterranean diet; LF, low-fat diet; BP, blood pressure; POMS, Profile of Mood States; SF-36, Short Form-36 Health Survey; WFR, weighed food record; CRP, C-reactive protein; RBCFA, red blood cell fatty acids

Participants will attend a pre-baseline appointment at the SIHR CTF where the study will be explained and informed consent will be obtained by study personnel (Appendix 7). Instructions and equipment will be given for the collection of home measures, including blood pressure, SF-36, POMS and WFR. Participants will then return 1 week later for week 0 assessments.

Clinic assessment visits will take place at baseline of the first diet (week 0), at the end of the first diet (week 8), at baseline of the second diet, after the 8-week washout period (week 16), and at the end of the second diet (week 24). Data for home measures will be collected by participants in the week prior to each of these visits.

At clinic assessment visits participants will be fasted from food, beverages (excluding water), alcohol and caffeine for 12 h. Clinic assessment visits will include measurement of blood pressure, body anthropometry, DEXA and collection of fasted blood samples. At weeks 0 and 16 participants will be allocated to their diet and meet with a dietitian to discuss the dietary guidelines. Participants will then be given a continental breakfast before cognitive tasks are administered. To minimise the impact and influence of external variables, cognitive testing conditions will be rigorously controlled and standardised as outlined by [70]. All cognitive testing sessions will take place between 9:30 am and 12:00 pm. To limit the impact of food intake on cognitive performance, participants will consume the same breakfast before each cognitive session.

If participants have performed a strenuous level of non-habitual exercise in past 10 h, not had an adequate amount of sleep, or are unusually tired cognitive assessments will be rescheduled. Temperature and noise of the cognitive testing environment will be controlled in order to reduce distraction and test administration will be standardised through the use of a testing script provided by Cambridge Cognition. Participants will commence the dietary intervention on the day following week 0 and week 16 visits, and will commence the washout period on the day of the week 8 visit.

Between weeks 0 and 8, and 16 and 24 participants will attend bi-weekly dietetic visits at the SIHR CTF. In the final dietetic visit of each diet phase, and at week 15, participants will be provided with equipment for the collection of home measures to be returned at their next clinic assessment visit.

Volunteers will be instructed to continue any habitual exercise and medications for the duration of the trial. Changes to exercise and medications will be monitored and recorded at bi-weekly dietetic visits and clinic assessment visits by the investigators.

### Statistical analysis

Statistical analyses will be conducted using SPSS for Windows, version 21.0 (SPSS Inc., Chicago, IL, USA) and Stata (version 14.2, StataCorp, College Station, TX, USA). Data will be presented as means ± standard deviation (SD) for descriptive statistics and as means ± standard error (SEM) for reporting estimated effects. All tests will be 2-tailed with *p*-values <0.05 deemed statistically significant.

Based on power calculations, a sample size of 31 volunteers is required to detect a clinically relevant difference of 2.5 mmHg in home blood pressure, the primary outcome measure, with power of 90%. This calculation accounts for a total of 54 readings (three readings taken three times per day for 6 days) at each time point, a within-group standard deviation of 14 mmHg, a within-subject repeated measures correlation of *r* = 0.6 and a between-phase within-subject correlation of *ρ* = 0.5. The correlation (ρ) and use of a cross-over design reduces the number of required participants by a factor of (1 − ρ)/2 = 4 [153] i.e., from approximately *n* = 124 for a parallel group design using ANCOVA (*n* = 62 per group) to *n* = 31 subjects in total.

Baseline demographic, cardiometabolic, cognitive, well-being and dietary characteristic data will be compared for those who complete the study and those who withdraw using independent t-test and chi-square tests, depending on the type of variable and distribution of data.

The primary analysis will be performed on a per protocol basis including only those subjects who complete both trial phases. A linear mixed effects model will determine the difference in each outcome between dietary interventions and will measure both between and within subject effects for cardiometabolic and cognitive outcomes. If a significant change is detected for cognitive outcomes a hierarchical regression will include cardiometabolic outcomes to assess their meditating effects. A sensitivity analysis will include weight loss, change in physical activity, medications and supplements as these may cause time-varying confounding should they differ between groups in the second dietary phase. Further, carryover and treatment-period effects will be assessed by including treatment*phase and treatment*order interaction terms. A diet*period*energy intake interaction term will be included to determine any significant changes between diets in relation to total energy intake, macronutrient intake and micronutrient intake. As an additional sensitivity analysis we will also include subjects that did not complete the trial or were not included in the per protocol analysis due to inadequate adherence (<75%). For missing data the linear mixed effects models will estimate unbiased effects as opposed to multiple imputation.

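### The 90% power stated for 31 participants at 2.5 mmHg does not follow from the printed inputs and is probably overstated

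*Protocol article*

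**What the plan says.** All of this stands in the Statistical analysis section of the protocol article.

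- Target: "a sample size of 31 volunteers is required to detect a clinically relevant difference of 2.5 mmHg in home blood pressure". The power is set at 90%.
- Test: "All tests will be 2-tailed with *p*-values <0.05 deemed statistically significant".
- Correlations used: ρ = 0.5 across the two phases in the same person, and "a within-subject repeated measures correlation of *r* = 0.6".
- Spread used: "a within-group standard deviation of 14 mmHg".
- Number of home measurements used: "a total of 54 readings (three readings taken three times per day for 6 days) at each time point".
- Step to the crossover: it is said that "use of a cross-over design reduces the number of required participants by a factor of" a quantity given as (1 − ρ)/2, whose value is printed as 4. The starting point is about 124 participants (62 per group), labelled as being "for a parallel group design using ANCOVA", and the end point is 31 in total.

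Table 1 repeats 31 as the target sample size and gives recruitment as complete. The paragraph does not say whether the SD, r and ρ describe single readings or 54-reading means. It gives no separate correlation between baseline and end of phase, and does not say whether ρ is before or after baseline adjustment.

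**The concern.** Three things look wrong. The base of 62 per group does not come out of the inputs listed beside it. The factor (1 − ρ)/2 converts an unadjusted parallel trial to a crossover, but here it is applied to an ANCOVA size, from which baseline adjustment has already removed within-person correlation. And the printed value of the factor is its reciprocal.

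Home systolic pressure is the only primary outcome, and this paragraph is the only justification of its sample size. If the trial finds no difference, the stated 90% would support reading that result as good evidence against 2.5 mmHg. That reading is only as sound as the calculation.

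**Working it through.** **Inputs** (all from the Statistical analysis section): δ = 2.5 mmHg, two-sided 5%, 90% power, SD 14 (variance 196), 54 readings per time point, r = 0.6, ρ = 0.5. K = (1.960 + 1.2816)² = 10.507 and δ² = 6.25. Compound symmetry is assumed. Power figures use the normal approximation unless marked t.

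**1. The last step reproduces.** (1 − 0.5)/2 = 0.25 and 124 × 0.25 = 31. The printed 4 is 1/0.25.

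**2. The base of 62 per group does not.** Let v = (1 + 53 × 0.6)/54 = 0.6074. The variance of a 54-reading mean is 196 × 0.6074 = 119.05 (SD 10.91). With a pre-post correlation c between single readings, the ANCOVA residual variance is 196 × (v − c²/v), and n per group = 2K × variance/δ².

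| Case | Variance | n per group |
|---|---|---|
| 54-reading mean, no baseline | 119.05 | 401 |
| ANCOVA, c = 0.5 | 38.4 | 130 |
| ANCOVA, c = 0.6 | 2.89 | 10 |
| ANCOVA, c = 0.558 (not stated) | 18.44 | 62 |

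The value 0.558 between readings is 0.558/0.6074 ≈ 0.92 between means. Applying 0.6 or 0.5 as the pre-post correlation of the means gives 257 or 301 per group. A value of 62 can be hit with unequal counts, such as 4 readings before and 54 after at r = 0.6, but that contradicts 54 at each time point.

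**3. The crossover factor.** For unadjusted data, total parallel N is 4Kσ²/δ² and crossover N is 2Kσ²(1 − ρ)/δ², so the ratio is (1 − ρ)/2. Starting from an ANCOVA size, the ratio depends on what ρ means.

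- ρ = 0.5 remains after baseline adjustment: variance of the difference is 2 × 18.44 × 0.5 = 18.44, SD 4.29, N = 31. The quartering is then correct.
- ρ = 0.5 is raw and also equals the pre-post correlation, with no baselines used in the crossover: ratio (1 − ρ)/[2(1 − ρ²)] = 1/[2(1 + ρ)] = 1/3, so 124/3 = 41.3, about 42. Power with 31 is about 80%.
- ρ = 0.5 is raw and baselines are used: the correlation left after adjustment is about 0.08 (reading-level pre-post and between-phase correlations both 0.5) to 0.125 (mean-level 0.6 and 0.5). N = 62 × (1 − 0.08) ≈ 57 down to 62 × (1 − 0.125) ≈ 54.
- No correlation left after adjustment: N = 62, and power with 31 is 63% (60% by t).

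**4. Direct crossover calculation**, N = K × Var(difference)/δ², on end-of-phase means:

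| Meaning of the inputs | SD of difference | N | Power with 31 (normal / t) |
|---|---|---|---|
| r and ρ both between readings: 2 × 196 × (0.6074 − 0.5) = 42.1 | 6.49 | 71 | 57% / 55% |
| ρ between phase means: 2 × 119.05 × 0.5 = 119.05 | 10.91 | 201 | 25% / 24% |
| SD 14 already that of the mean: 2 × 196 × 0.5 = 196 | 14.0 | 330 | 17% / 16% |

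On the first row, 31 has 90% power for 3.24 × 6.49/√31 ≈ 3.8 mmHg.

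**5. The same with baseline adjustment** (first row above, pre-post reading correlation c). The adjusted variance is 42.1 − [2 × 196 × (c − 0.5)]²/42.1.

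| c | Variance | N | Power with 31 |
|---|---|---|---|
| 0.50 | 42.1 | 71 | 57% |
| 0.55 | 33.0 | 55.4 | 68% |
| 0.58 | 18.75 | 31.5 | about 90% |
| 0.60 | 5.6 | 9.4 | above 99% |

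**6. What 31 requires.** SD of the within-person difference = 2.5 × √31/3.2415 = 4.29 mmHg. The paragraph does not state this.

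**The case against.** The strongest reply is that the paragraph names two different correlations. Set against a between-phase ρ, the repeated-measures r = 0.6 can be read as covering all readings within a phase, baseline included. On that reading ANCOVA needs about 10 per group, the baseline-adjusted crossover about 10 in total, and 31 is ample. The trial does measure home pressure at the start and end of both phases, so calculations on end-of-phase values alone leave information out. If ρ is meant after baseline adjustment, the quartering is correct. The factor carries a citation numbered 153, whereas the other citations in the article run to 76. That suggests condensation from a longer document that may give the details. The misprinted 4 changes nothing downstream.

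Much of this stands. A reader might infer that the trial certainly lacks its stated power, or that within-person correlation is certainly counted twice. The document supports neither as a fact, because it leaves open the level of the SD, r and ρ and whether ρ is adjusted. A flat restatement as 55% power would be equally unsupported.

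The reply does not rescue the printed derivation. The reading that makes 31 ample gives 10 per group, not 62, so it contradicts the paragraph's own intermediate figure. A longer source might supply the missing correlation, but what is printed does not lead to what is concluded.

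**Conclusion.** The claim of 90% power for 2.5 mmHg with 31 participants is not supported by its stated inputs. The per-group base is 401, 130 or 10 depending on a correlation that is not given, and 62 needs about 0.558 for it.

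The claim is probably overstated. Even granting 62 per group, a raw ρ means roughly 42 to 62 are needed and 31 gives about 63–80% power. Taken directly on end-of-phase means, power is about 55–57% with both correlations at reading level and about 24% with ρ between phase means. In the baseline-adjusted calculation, 90% with 31 needs a pre-post reading correlation near 0.58, which is 0.58/0.6074 ≈ 0.95 between means, while the between-phase value is 0.5/0.6074 ≈ 0.82.

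That possibility is not excluded, so underpowering and double counting remain conditional. What does not depend on the reading is that the printed inputs do not yield 62, and that (1 − 0.5)/2 is 0.25. These results assume compound symmetry and no dropout.

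**What to change.** Replace the sample-size paragraph with a direct crossover calculation, N = (z₀.₉₇₅ + z₀.₉₀)² × SD_diff²/δ², and state:

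- whether SD 14, r = 0.6 and ρ = 0.5 each describe single readings or 54-reading means;
- the correlation between baseline and end of phase, and its source;
- whether ρ is before or after baseline adjustment;
- the resulting SD of the within-person difference. If there is evidence for about 4.3 mmHg, give that as the input.

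Then restate the power for 2.5 mmHg, or the difference detectable with 90% power, that 31 delivers on those inputs. Give a range if the pre-post correlation is uncertain. Correct the value of (1 − ρ)/2 to 0.25, that is, a reduction by a factor of 4.

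The cost is one rewritten paragraph. No extra recruitment is asked for. The downside is that the stated power may become less favourable.

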Date of first enrolment	15 February 2017
Target sample size	31
Recruitment status	Complete
Primary outcome(s)	Home measured systolic blood pressure
Key secondary outcomes	Body mass index (BMI), body composition, fasting blood lipids, C-reactive protein, fasting plasma glucose, fasting serum insulin, erythrocyte fatty acids, cognitive function, psychological health and well-being, and dementia risk.

To meet eligibility criteria, volunteers must have elevated systolic blood pressure above 120 mmHg and at least two other risk factors for CVD, including: a BMI ≥ 25 kg/m2; elevated fasting total cholesterol (≥5.5 mM), triglycerides (≥2.0 mM), low-density lipoprotein (LDL) (≥3.5), or low levels of high-density lipoprotein (HDL) (≤0.9 for men and ≤1.0 for women); impaired fasting glucose tolerance (between 6.1 and 7.8 mmol/L); and/or a family history (up to one generation) of CVD or type 2 diabetes mellitus (T2DM). Exclusion criteria include: antihypertensive medication; smoking; current CVD or angina; current or recent (within 6 months) malignancies; respiratory disease; gastrointestinal disease; kidney disease; T2DM; a current or previous traumatic head or brain injury; a current neurological or psychiatric condition; antidepressant or anxiety medication; a current diagnosis of Alzheimer’s disease or dementia; or supplemental omega-3 > 1000 mg daily.

Eligibility will be assessed through a diet and lifestyle questionnaire (DLQ) and screening visit at the Sansom Institute for Health Research Clinical Trial Facility (SIHR CTF), Adelaide, South Australia. The DLQ includes medical history, medications and supplements, family medical history, and dietary aversions, allergies and intolerances. Volunteers deemed eligible on the basis of their DLQ will be screened to measure systolic blood pressure, diastolic blood pressure, heart rate, height and weight, fasting cholesterol and fasting glucose. The Addenbrooke’s Cognitive Exam-Revised (ACE-R) will also be administered to detect pre-existing dementia and mild cognitive impairment (MCI).

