#### Dietary adherence

A 15-item Mediterranean diet adherence survey and a 9-item low-fat diet adherence survey (Appendix 6) will be administered to participants bi-weekly to capture generalised patterns of food consumption during each of the intervention phases. Each survey has been adapted from the PREDIMED study to reflect an Australian food supply and national guidelines for alcohol consumption. While on the Mediterranean diet, participants will also complete a semi-quantitative weekly checklist (Appendix 3, described above). Adherence to the dietary phase will be determined at each bi-weekly visit, where participants must meet a minimum adherence requirement of 75%, as determined by checklists. If participants scoring below 75% are unable to increase their adherence in the next 2 weeks they will be excluded from the study.

To determine the impact of dietary adherence on outcomes an overall Mediterranean diet score [15, 26] will be calculated using data from a 3-day weighed food record (WFR) completed by participants before and at the end of each intervention phase. Further, erythrocyte fatty acids will provide a biological measure of dietary adherence at the end of each intervention phase.

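### The 31 participants needed for 90% power are also the whole enrolment target, so any loss from the completers-only primary analysis takes power below 90%

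*Protocol article*

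**What the plan says.** The Statistical analysis section of the protocol article states that "a sample size of 31 volunteers is required" "to detect a clinically relevant difference of 2.5 mmHg in home blood pressure", "with power of 90"%. It lists what the calculation takes into account: 54 readings per time point, a standard deviation of 14 mmHg, a repeated-measures correlation of 0.6, a between-phase correlation of 0.5, and a cross-over reduction from about 124 participants to 31. Loss to follow-up and non-adherence are not on that list.

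Table 1, under Recruitment, gives "Target sample size" as 31 and recruitment status as complete.

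The same Statistical analysis section makes the primary analysis per protocol, "including only those subjects who complete both trial phases". It places participants with adherence below 75% outside that analysis. Under Dietary adherence, participants below 75% at a bi-weekly visit have two weeks to improve. If they do not, "they will be excluded from the study".

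The plan foresees such losses. Completers are to be compared with those who withdraw, and a sensitivity analysis brings back non-completers and participants left out for poor adherence.

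**The concern.** Power is quoted on all 31 participants, but the primary analysis is defined on a subset of them. The number required and the number targeted are the same, so the design has no margin. Each participant must follow two diets over 24 weeks, with an adherence threshold applied at every bi-weekly visit, and the plan itself expects some to fall out.

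What is at stake is how the result is read. A null result would be reported as coming from an analysis with 90% power when the analysis actually run had less.

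**Working it through.** **Inputs.** Two-sided alpha 0.05, power 90%, difference 2.5 mmHg and n = 31 come from the Statistical analysis section. The target of 31 comes from Table 1. The loss rates below are my assumptions, since the article gives none.

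**1. The plan's own last step.** The cross-over multiplier is (1 − ρ)/2 = (1 − 0.5)/2 = 0.25, and 124 × 0.25 = 31.0. The 31 is therefore exact, with no rounding up and no inflation for loss. (The article writes this factor as equal to 4, which is the reciprocal of 0.25. The 31 is unaffected.)

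**2. What is taken as given.** I could not reproduce the preceding figure of 62 per group from the listed inputs at 90% two-sided. With the usual repeated-measures ANCOVA variance, 54 readings before and 54 after give about 10 per group. A post-only analysis of 54 readings gives about 400. That is a separate matter. Here I accept 90% at n = 31 and ask only what losses do to it.

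**3. Implied standard deviation of the within-person difference.** z₀.₉₇₅ + z₀.₉₀ = 1.960 + 1.2816 = 3.2415. SD = 2.5 × √31 / 3.2415 = 4.294 mmHg.

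**4. Power with n analysed.** Power = Φ(3.2415 × √(n/31) − 1.960).

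| Analysed | Lost | Argument of Φ | Power (normal) |
|---|---|---|---|
| 31 | 0 | 1.282 | 90.0% |
| 30 | 1 (3%) | 1.229 | 89.0% |
| 28 | 3 (10%) | 1.121 | 86.9% |
| 25 | 6 (19%) | 0.951 | 82.9% |
| 24 | 7 (23%) | 0.892 | 81.4% |
| 23 | 8 (26%) | 0.832 | 79.7% |
| 22 | 9 (29%) | 0.771 | 78.0% |

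**5. Check with a t reference.** This uses a non-central t with n − 2 degrees of freedom. The standard deviation has to be recalibrated so that n = 31 still gives 90%, which makes it 4.149. Power is then 86.6% at 28, 82.2% at 25 and 76.7% at 22. Carrying over the normal-theory 4.294 would give only 88.0% at n = 31 with nobody lost, so about two points of any apparent fall would come from changing the reference distribution and not from attrition.

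**6. How likely is no loss?** If each participant independently has a 5% chance of loss, the chance that all 31 remain is 0.95³¹ = 20%. At 10% it is 0.90³¹ = 3.8%, and at 20% it is 0.80³¹ = 0.1%.

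**7. Size of the missing allowance.** To keep 31 analysable, N = 31/(1 − d): 31/0.90 = 34.4, so 35 at 10% loss, and 31/0.80 = 38.75, so 39 at 20%. This only shows scale. It is not a proposal to enrol more.

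**The case against.** The strongest reply is that 31 may mean the evaluable number. The article says that 31 are required, not that 31 will be randomised, and a margin could sit in a fuller protocol. Table 1 answers this: it gives 31 as the target sample size. The point therefore rests on stated items that do not fit together, and not on detail an article would normally leave out. It remains true that the article does not report how many were actually randomised.

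The second reply is that the effect is small and depends on assumed losses. This largely stands. Early losses cost about one point each, and power stays near 80% until about eight of 31 are gone. A reader might infer from a requirement of zero loss that power collapses once anyone drops out. The figures do not support that reading.

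Third, a reader might infer that every participant who falls below 75% adherence is dropped at once. The Dietary adherence section allows two weeks to recover, and the plan provides food and regular dietitian contact to support retention. These measures may limit losses, but no expected rate is given. The sensitivity analysis that brings excluded participants back does not restore power to the primary analysis.

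Finally, a reader might infer that the primary analysis has to move to everyone randomised. The power statement does not depend on that. The choice of population concerns bias and the estimand, and it should be argued on those grounds.

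**Conclusion.** The point holds as a moderate overstatement of power. The required number and the target are both 31, the calculation lists no allowance for loss, and the primary analysis leaves out non-completers and persistent non-adherers. By the plan's own figures, 90% applies only if nobody is lost.

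With 25 to 28 analysed, power is about 83% to 87%; with 22 it is about 78%. These values depend on two things: assumed loss rates, because the article gives none, and acceptance of 90% at n = 31, which the listed inputs do not reproduce. They illustrate the effect of loss and do not re-estimate the trial's true power.

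**What to change.** In the Statistical analysis section, state that 31 is the number to be randomised. Replace the single 90% figure with power for the expected evaluable number, naming the loss assumed. For example: with 25 to 28 participants in the per-protocol analysis, power to detect 2.5 mmHg is about 83% to 87%, taking the original calculation as given. If the derivation of 62 per group is revisited, recompute these values from the corrected baseline.

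Do not enrol more participants on this account, since Table 1 records recruitment as complete. The change takes a sentence, and the price is a slightly less favourable stated power. It requires no change to the analysis population.

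### The primary test of a difference is confined to adherent completers, a set formed after randomisation, and the wider analysis is kept as a sensitivity check

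*Protocol article*

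**What the plan says.** The Statistical analysis section fixes the primary set: "The primary analysis will be performed on a per protocol basis including only those subjects who complete both trial phases". Adherence is a second filter, which emerges only where the section sets out its further checks: "we will also include subjects that did not complete the trial or were not included in the per protocol analysis due to inadequate adherence". The section then adds: "For missing data the linear mixed effects models will estimate unbiased effects as opposed to multiple imputation". The hypothesis test is a conventional one for a difference: "All tests will be 2-tailed with *p*-values <0.05 deemed statistically significant". No non-inferiority or equivalence margin appears anywhere in the article.

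The adherence filter is defined under Dietary adherence. At each bi-weekly visit "participants must meet a minimum adherence requirement of 75%, as determined by checklists", and "If participants scoring below 75% are unable to increase their adherence in the next 2 weeks they will be excluded from the study". On the instrument, the same section says: "While on the Mediterranean diet, participants will also complete a semi-quantitative weekly checklist". The Dietetic counselling section likewise describes the checklist among the Mediterranean diet materials. For the low-fat phase it lists guidelines, education on fat content and a label-reading guide. A 9-item low-fat adherence survey exists, but the 75% threshold is not tied to it.

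**The concern.** Whether a participant finishes both phases, and whether he or she reaches 75% adherence, is known only after allocation. Either can depend on the diet being followed, on how well it suits the person and on how blood pressure responds. For a test of a difference, a primary set chosen by such events tends to favour a diet that works in those able to follow it. The usual reason for giving a per protocol set equal or greater weight, a non-inferiority claim, does not apply here.

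The adherence filter may also be lopsided. If checklists are used only in the Mediterranean phase, poor adherence to that diet removes a person and poor adherence to the low-fat diet may not.

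At stake is what the headline result means. The Abstract says that findings may inform individuals, clinicians and public health policy. An effect in adherent completers is a narrower quantity than the effect of being assigned the diet.

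**Working it through.** **Which set answers which question.** The relevant statements, side by side:

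- Primary: completers of both phases, with those below 75% adherence left out (Statistical analysis).
- Sensitivity: the above plus non-completers and non-adherers (Statistical analysis).
- Persistent non-adherers: removed from the study, not only from the analysis (Dietary adherence).

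The third statement limits the second. If home blood pressure is not collected after removal, the sensitivity analysis has only the data gathered before it, and it cannot fully restore the randomised set. The article does not say whether measurement continues.

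**What pairing protects.** In a two-period cross-over the completer estimate is a mean of within-person differences, so stable traits cancel. It equals the effect in all randomised only if the mean diet difference is the same in those kept and those lost. Loss that depends on response, or that differs by sequence, breaks this.

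**Size, first scenario (assumed values).** Let *p* be the proportion excluded and *f* the fraction of the effect they have. Take 2.5 mmHg, the target difference in Statistical analysis, as the effect in those retained. Then

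effect in all randomised = 2.5 × [1 − *p*(1 − *f*)].

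| Excluded *p* | *f* = 0.5 | *f* = 0 |
|---|---|---|
| 10% | 2.5 × 0.95 = 2.375 | 2.5 × 0.90 = 2.25 |
| 20% | 2.5 × 0.90 = 2.25 | 2.5 × 0.80 = 2.00 |
| 30% | 2.5 × 0.85 = 2.125 | 2.5 × 0.70 = 1.75 |

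The range is about 2.4 to 1.75 mmHg. The documents supply only the 2.5; *p* and *f* are assumptions.

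**Size, second scenario (assumed values).** Let the true individual diet difference vary with SD 2 or 4 mmHg. Let the log-odds of staying rise by 0.5 or 1.0 per SD of benefit, with 10%, 20% or 30% lost overall. Simulation moves the completer mean towards greater benefit by 0.10 mmHg (SD 2, 10% lost, weaker selection) up to 1.02 mmHg (SD 4, 30% lost, stronger selection).

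**Precision.** The plan's own last step reproduces: 124 × (1 − 0.5)/2 = 31. The 62 per group behind it is taken as given here; whether it follows from the stated inputs is a separate matter. With 90% power at 31, two-sided 0.05, the implied SD of the paired difference is 2.5 × √31 / (1.96 + 1.2816) = 4.29 mmHg. Losses of 10%, 20% and 30% leave about 28, 25 and 22 completers, and by the normal approximation power is about 87%, 83% and 78%. Most of this loss would remain under the wider analysis, because one-phase participants add little to a within-person contrast. It shows how few participants the primary result could rest on; it is not an argument for one set over the other.

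**The case against.** The strongest defence is that the stated aim, to evaluate the benefits of the diet, is partly an efficacy question. Adherent completers are a reasonable population for that, and each serves as his or her own control. The wider analysis is prespecified, and completers will be compared with withdrawals at baseline, so readers would see both results. One-phase participants carry only between-person information on the diet contrast, so little efficiency is lost by leaving them out. All of this stands as mitigation. It does not justify giving the selected set the primary role in a test of a difference, and a baseline comparison cannot show selection on response.

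Four stronger readings are tempting and are not supported:

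- *That the missing-data sentence contradicts the primary set.* It directly follows the sentence that adds back non-completers and non-adherers, and it can be read as describing that analysis, or missed outcomes within completers. What remains is that it claims unbiasedness without the condition of missing at random.
- *That the effect would be overstated by a fixed proportion*, for instance 25% (2.5 against 2.0 mmHg). That is one cell of the table. It assumes no effect at all in the excluded, although adherence below 75% is not zero adherence, and it compares two different estimands.
- *That the protocol expects its own diet to be hard to follow.* The Background says this of red meat restriction in the traditional diet. The tested diet adds pork to ease that, with foods supplied and regular dietitian contact.
- *That changing the order is a matter of wording only.* It is not, if blood pressure stops being measured once a participant is removed.

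**Conclusion.** The concern holds. The article itself fixes a primary set selected by two post-randomisation criteria for a two-sided test of a difference, without giving a reason, and nothing elsewhere reverses it. This is not a detail left to an unseen analysis plan. The estimate applies to adherent completers, and it is open to bias if loss depends on response or sequence. The documents give no loss rate and no effect in those lost, so the size is unknown. Under the assumptions shown, a 2.5 mmHg effect in the retained would correspond to about 2.4 to 1.75 mmHg in all randomised.

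That the adherence filter acts on one diet only is possible, not established: the article describes the checklist only for the Mediterranean phase, and the full materials may contain a low-fat counterpart. A reader might also infer that the cross-over comparison is invalid. It is not; pairing still removes confounding by stable traits. The point is a cheap improvement to the headline analysis.

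**What to change.** 1. Exchange the roles of two analyses already planned. Primary: the linear mixed model on all randomised participants with available home systolic blood pressure, by randomised sequence and regardless of adherence. Secondary: the per protocol set. Participants with no blood pressure after allocation would still be absent, so their number should be reported by sequence.
2. Replace the unconditional claim of unbiasedness with a statement that the mixed model is valid under missing at random.
3. Reconcile Dietary adherence, which removes persistent non-adherers from the study, with Statistical analysis, which plans to analyse them, on whether outcome measurement continues after non-adherence. Without those data the model relies on similar participants who stayed, and it can only partly restore the randomised set.
4. State which instrument determines the 75% threshold in the low-fat phase.

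Cost: items 1, 2 and 4 are changes of text. Item 3 may require some outcome collection after exclusion. The primary estimate may be somewhat diluted relative to the per protocol one, which would still be reported.
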